### Randomization and group allocation

2.4

This study adopts a cluster randomized design, with classes serving as the unit of randomization. The randomization process will be conducted in two stages, as follows:

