#### Stage 1: selection of eligible classes

2.4.1

First, among a total of 16 classes that meet the inclusion criteria within the school, 4 target classes will be randomly selected using Microsoft Excel. The procedure is as follows: a new worksheet will be created, with Column A assigned numbers from 1 to 16 as unique identifiers for each class. In Column B, the formula = RAND() will be used to generate random numbers for each class. These random numbers will then be copied and pasted as values to prevent subsequent changes. All classes will then be sorted in ascending order based on the values in Column B, and the first 8 classes will be selected as the study sample.

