#### Stage 2: random allocation to intervention groups

2.4.2

The selected 4 classes will then be randomly assigned to intervention groups using Excel. Specifically, in a new worksheet, Column A will be assigned numbers from 1 to 4 as unique identifiers for the included classes. In Column B, the = RAND() function will again be used to generate random numbers, which will subsequently be copied and pasted as values. The classes will then be sorted in ascending order based on Column B. According to the sorted order, classes will be sequentially allocated into four intervention groups: the 1st classes will be assigned to Intervention Group 1, the 2nd classes to Group 2, the 3rd classes to Group 3, and the 4th classes to Group 4. The class identifiers will remain in Column A, while the allocation will be determined by the ranking in Column B.

To ensure the validity of randomization, a single-blind design will be employed, whereby participants will be unaware of their group assignments, while only the intervention implementers will have access to the allocation information. In the event of a serious adverse event or when knowledge of group allocation is required to ensure participant safety, unblinding will be requested by the principal investigator and implemented after approval by the Ethics Committee, with the entire process fully documented. To maintain allocation concealment, the sealed envelope method will be used. Specifically, four opaque envelopes will be prepared, each labeled with a unique identifier corresponding to the class identifiers in Column A. Inside each envelope, a slip indicating the assigned group will be placed. The allocation information will remain sealed and concealed until the commencement of the intervention.

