### Sample size calculation

2.10

This study is a two-factor factorial cluster randomized controlled trial, with “CPR knowledge and skills scores” as the primary outcome. Based on the literature, a significance level of 5% (*α* = 0.05) and a statistical power of 80% (*β* = 0.20) were adopted. Sample size estimation was informed by data from previous studies. It was assumed that the mean total CPR score (combined knowledge and skills score rate) would be 80% in the intervention group and 65% in the control group, with a standard deviation of 15% in both groups, corresponding to an effect size of *d* = 1.0. Assuming a 15% difference in the primary outcome (main effect), G*Power 3.1 was used for sample size calculation, indicating that a total of 128 participants would be sufficient for multivariate regression analysis (effect size = 0.25, power = 0.80, critical *F* = 3.921). Considering a potential attrition rate of 20%, the final minimum sample size was set at 160 participants. This study also takes into account the design effect resulting from the correlation among subjects within clusters. The design effect is calculated using the formula DE = 1 + (m − 1)*ρ*, where m represents the average number of subjects per cluster, and ρ represents the intracluster correlation coefficient (ICC) (17). In cluster randomized trials, the design effect is commonly used to adjust the sample size required for an individual randomized trial to the sample size required for a cluster-randomized design. The final minimum sample size for this study was set at 160 participants, which represents a 25% overall inflation factor added to the 128 participants required at the individual level. This inflation factor accounts for both the cluster-randomized design effect and the potential impact of dropouts or invalid data. Based on the average cluster size in this study and the ICC estimated from previous similar studies, the design effect did not exceed 1.25 (18). Therefore, after adjusting for the design effect, a sample size of 160 participants (selecting 4 classes, with 40 participants per class) would still provide no fewer than 128 valid cases, thereby meeting the requirements for testing the primary effect.

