### Data analysis plan

2.13

This study adopted a 2 × 2 factorial cluster randomized controlled trial design, with class as the unit of random allocation and individual students as the unit of analysis. All statistical analyses will account for clustering at the class level and the correlation among repeated measurements from the same participant. Three analysis sets will be predefined: the full analysis set, the per-protocol set, and the safety analysis set. The full analysis set will serve as the primary analysis population and will include all randomized participants, who will be analyzed according to their originally assigned groups, following the intention-to-treat principle. Participants will not be excluded from the primary analysis because of intervention non-completion, absence from training sessions, or withdrawal during the intervention period, nor will their originally assigned group be changed. The per-protocol set will be used for robustness analyses and will include only participants who complete the predefined core intervention components and complete the primary outcome assessment. The safety analysis set will include participants who receive at least one intervention session or participate in at least one training activity, and will be used for descriptive analyses of adverse events and safety-related information. Two binary intervention factors are specified: Factor 1, initial training method, including lecture-only training versus lecture plus manikin practice; and Factor 2, booster reinforcement method, including traditional review versus scenario-based simulation. The four factorial groups correspond to Classes 13, 1, 10, and 12, respectively.

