Continuous outcomes will be analyzed using linear mixed-effects models. Binary outcomes will be analyzed using generalized linear mixed-effects models, and ordinal outcomes will be analyzed using ordinal logistic mixed-effects models. The models will include both fixed and random effects. Fixed effects will include the two intervention factors, time, the interaction between the two intervention factors, the interactions between each intervention factor and time, and the three-way interaction among the two intervention factors and time. When necessary, baseline outcome values and other prespecified covariates will also be included. Random effects will include a class-level random intercept to account for the correlation among students within the same class, as well as an individual-level random intercept to account for the correlation among repeated measurements from the same participant over time.

For repeated-measures data, within-participant correlation will be addressed through the inclusion of an individual-level random intercept. If the number of measurement time points and sample size allow, an unstructured covariance structure will be prioritized. If the model fails to converge or parameter estimates are unstable, compound symmetry or first-order autoregressive covariance structures will be considered as alternatives. The final model will be selected based on model fit indices and study design considerations. Model selection will consider the Akaike information criterion, Bayesian information criterion, model convergence, and the interpretability of parameter estimates.

Factorial effects will be analyzed according to the principle of interaction-first interpretation. For the primary outcome, the interaction between the two intervention factors and the three-way interaction among the two intervention factors and time within the repeated-measures framework will first be tested. If the interaction is statistically significant or shows a practically meaningful trend, simple-effects analyses will be conducted to estimate the effects of different intervention combinations at each time point. If no clear interaction is observed, the main effects of the two intervention factors will be interpreted. For intervention effects that vary over time, the interaction terms between intervention factors and time will be treated as key parameters for evaluating changes in intervention effects.

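### Each arm is one class, so the planned class random intercept, ICC and design effect cannot be estimated, and single-time-point effects cannot be separated from class

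*Protocol article*

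**What the plan says.** Section 2.4 makes the class the unit of randomisation: "This study adopts a cluster randomized design, with classes serving as the unit of randomization". Section 2.4.2 continues: "The selected 4 classes will then be randomly assigned to intervention groups using Excel", and then "the 1st classes will be assigned to Intervention Group 1, the 2nd classes to Group 2, the 3rd classes to Group 3", with the fourth going to Group 4. Section 2.10 gives the same layout ("selecting 4 classes, with 40 participants per class"), and section 2.13 names the classes: "The four factorial groups correspond to Classes 13, 1, 10, and 12, respectively".

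The one discordant text is in section 2.4.1. It opens with "4 target classes will be randomly selected using Microsoft Excel" and ends with "the first 8 classes will be selected as the study sample".

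For the analysis, section 2.13 promises that every analysis will allow for class-level clustering. The mixed model has fixed effects for Factor 1, Factor 2, time, all two-way interactions and the three-way interaction. On top of these, "Random effects will include a class-level random intercept to account for the correlation among students within the same class", together with a student-level random intercept. The same section plans to calculate the ICC and design effect from the trial data. The limitations in the Discussion do not mention that each arm is a single class.

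**The concern.** A class random intercept measures how much classes differ when they receive the same treatment. With one class per arm and a fixed effect for every arm at every time point, the planned model contains no two classes sharing a fitted mean, so nothing is left from which to estimate that variance.

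At a single time point, a difference between classes in class teacher, grade or ability would be read as a training effect. If the software sets the class variance to zero, students are analysed as though individually randomised and the standard errors are too small. If it stops at some other value, the standard errors depend on that arbitrary value. The stated aim of separating the main effects and interaction of the two components rests on these contrasts.

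**Working it through.** **The plan's own sample size.** Inputs from section 2.10: f = 0.25, α = 0.05, power 0.80. With numerator df 1 and four groups, the noncentral F gives N = 128, power 0.801 and critical F 3.918 on 124 df (stated: 3.921). Then 128/(1 − 0.20) = 160 and 128 × 1.25 = 160. Both figures reproduce. Neither calculation depends on the number of classes per arm.

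**Class-level degrees of freedom.** At any time point there are 4 class means. The intercept, Factor 1, Factor 2 and Factor 1 × Factor 2 take 4 parameters, so 4 − 4 = 0 remain. Over five time points the fixed part has 4 × 5 = 20 parameters. For 4 classes × 40 students × 5 times, the fixed-effect matrix has rank 20, and it still has rank 20 after the class indicators are added. The class effects lie wholly within the span of the fixed effects.

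**Likelihood.** On a simulated data set with this structure (10 students per class), the REML log-likelihood was −67.599497 at class variances 0, 0.05, 0.25, 1 and 10. REML is flat, and ML favours zero. The class size does not affect the flatness.

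**What the unidentified variance does to standard errors.** I took 40 per class, residual variance 1 and student variance 0.5 (illustrative values).

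| Class variance | SE, Factor 1 effect at T1 | SE, Factor 1 effect on T1 − T0 |
|---|---|---|
| 0 | 0.194 | 0.224 |
| 0.05 | 0.296 | 0.224 |
| 0.2 | 0.487 | 0.224 |
| 1 | 1.019 | 0.224 |
| 5 | 2.244 | 0.224 |

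REML supports every row equally. The single-time-point SE is whatever the class variance is taken to be. The change contrast is unaffected, because a constant class effect cancels.

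**Type I error with class variance fixed at zero.** Take a Factor 1 main effect at one time point, two class means against two, no baseline correction, total variance 1 and m = 40. The true variance is ρ + (1 − ρ)/m, while the analysis uses (1 − ρ)/m. The test statistic is inflated by √(1 + mρ/(1 − ρ)), and the critical value on 156 df is 1.975.

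| ICC ρ | Inflation | 1.975/inflation | Type I error |
|---|---|---|---|
| 0.0064 | 1.121 | 1.761 | 8.0% |
| 0.01 | 1.185 | 1.667 | 9.8% |
| 0.05 | 1.762 | 1.121 | 26.4% |
| 0.10 | 2.333 | 0.847 | 39.9% |

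The first ICC follows from the protocol's design-effect ceiling: 0.25/(40 − 1) = 0.0064. The protocol states no ICC, so the other three are assumptions.

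**Early Factor 1 effect.** Factor 2 is the booster method, delivered in Phase 2, and T2 precedes the second training. Until then, two classes at each level of Factor 1 have had the same treatment. That leaves 4 − 2 = 2 class-level df in principle, but the planned model spends both on Factor 2 and the interaction.

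**The case against.** **Change from baseline protects the trial.** In part it does. The factor-by-time terms, which section 2.13 treats as key where effects vary over time, cancel any stable class difference when taken against T0, as the table of standard errors shows. Class-specific change over time remains confounded with arm, and a random intercept does not describe it. Section 2.13 also plans main effects and simple effects at each time point, which have no such protection unless baseline is adjusted for; that adjustment is planned only where necessary.

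**The early Factor 1 comparison has replication.** This stands. For that comparison the fault lies in the model rather than the design.

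**Instructors rotate across the four classes.** Section 2.11 says so, and this reduces confounding with the CPR instructor. It does nothing about class teacher, grade or ability.

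**The trial is a pilot.** Section 2.13 says so and stresses effect sizes and intervals. But it also keeps p < 0.05 as the criterion for significance, and section 2.10 claims enough cases to test the primary effect.

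**Clustering was allowed for in the sample size.** Inflating the number of students does not replicate classes, and 20% attrition alone already takes 128 to 160.

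**Perhaps there are eight classes.** Four classes are stated elsewhere in section 2.4.1 and in sections 2.4.2, 2.10 and 2.13. The 8 is best read as a drafting error to be reconciled, not as evidence of two classes per arm.

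**Conclusion.** The concern holds. With one class per arm and the fixed effects as planned, the class variance, ICC and design effect cannot be estimated separately from the intervention, and the statement that all analyses account for class clustering cannot be met. This follows from the stated layout and needs no assumed figure.

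A reader might infer that every intervention effect is fully confounded with class. The documents do not support that. Full confounding applies to main, interaction and simple effects at a given time point. Contrasts against T0 are exposed only to class-specific change, and Factor 1 at T1 and T2 has two classes per level.

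A reader might also infer that every test in the trial has a grossly inflated error rate. The 8% to 40% range applies only to an uncorrected main-effect test at one time point with class variance at zero and 40 students per class. At the protocol's own ceiling the figure is 8%; anything higher rests on an assumed ICC.

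**What to change.** In section 2.13:

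- Delete the class random intercept, the statement that all analyses account for class clustering, and the promise to calculate the ICC and design effect from these data.
- State, there and in the limitations, that class and arm cannot be separated.
- Base between-arm estimates on change from T0 or on baseline adjustment.
- Estimate the Factor 1 effect at T1 and T2 as two classes against two, without Factor 2 terms.
- Present results as pilot estimates limited to these four classes, with intervals inflated over an assumed ICC range and no claim that p < 0.05 shows efficacy.

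In section 2.4.1, give one number of classes. The cost is wording and weaker claims; no data collection changes.

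Section 2.13 already names the four classes, so allocation may be complete. Only if it is not, the 160 students could be spread over more of the 16 eligible classes. The scheduling cost is real, because training is delivered by class and the plan assumes 40 per class. It is also no guarantee of power. With 20% loss, ICC 0.05 (assumed), main-effect variance (ρ + (1 − ρ)/m) × 4/K for K classes of m completers, and K − 4 df:

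| Layout | Power at d = 1.0 | Power at d = 0.5 (f = 0.25) |
|---|---|---|
| 8 classes, 16 completers each | 0.89 | 0.37 |
| 16 classes, 8 completers each | 0.99 | 0.61 |

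Section 2.10 quotes d = 1.0 but obtains 128 from f = 0.25, so the effect size would have to be settled before choosing this route.

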**Discussion:**

This study applies a CPR training model integrating manikin-based practice and scenario-based drama review, and systematically evaluates the independent effects and interaction effects of different intervention components using a factorial design. The expected findings will provide more practical and effective intervention strategies for CPR training among middle school students, and offer empirical evidence for optimizing school-based first aid education systems and informing relevant policy development.

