Adjusted effect estimates and their 95% confidence intervals will be reported. For continuous outcomes, between-group mean differences or standardized effect sizes will be reported. For binary outcomes, odds ratios or relative risks with 95% confidence intervals will be reported. For ordinal outcomes, corresponding ordinal odds ratios will be reported. The intraclass correlation coefficient and design effect will be calculated to quantify clustering effects. The robustness of the results will be examined through per-protocol analysis and multiple imputation.

For missing data, the number, proportion, and reasons for missingness will first be reported by study group. If outcome data are missing, multiple imputation will be performed under the missing-at-random assumption. Each imputed dataset will be analyzed separately, and the estimates will then be pooled. To assess the potential impact of post-randomization differential attrition on the study conclusions, sensitivity analyses will be conducted. If there are apparent differences across study groups in intervention-period withdrawal rates, absence rates, intervention non-completion rates, or loss-to-follow-up rates, their potential contribution to selection bias and their possible influence on estimates of intervention effects will be discussed in the interpretation of the results.

Given that this is a pilot study, the sample size was primarily determined based on implementation feasibility. A lack of statistical significance in interaction tests will not necessarily rule out the presence of practically meaningful interaction effects. Therefore, the findings will be interpreted comprehensively by considering effect sizes, confidence intervals, intervention adherence, and implementation feasibility. All statistical tests will be two-sided, and a *p* value of < 0.05 will be considered statistically significant. Statistical analyses will be conducted using SPSS 27.0 and R 4.5.2 (packages lme4, emmeans, and mice).

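### Sections 2.10 and 2.13 give incompatible accounts of the trial's status and of how the 160 students were arrived at, and 2.10's claim that 160 is adequate fails on its own figures

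*Protocol article*

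**What the plan says.** Section 2.10 (Sample size calculation) presents a formal power calculation:

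- Error rates: "a significance level of 5% (*α* = 0.05) and a statistical power of 80% (*β* = 0.20) were adopted".
- Planning values: means of 80% and 65%, "with a standard deviation of 15% in both groups, corresponding to an effect size of *d* = 1.0".
- Software entry: "effect size = 0.25, power = 0.80, critical *F* = 3.921", "indicating that a total of 128 participants would be sufficient for multivariate regression analysis".
- Inflation: 20% attrition takes the minimum to 160. The same 25% increase over 128 is then said to cover both the design effect and dropout or invalid data. The design effect is said not to exceed 1.25; no intracluster correlation (ICC) is given.
- Conclusion: four classes of 40 "would still provide no fewer than 128 valid cases, thereby meeting the requirements for testing the primary effect".

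The last paragraph of section 2.13 (Data analysis plan) gives a different account: "Given that this is a pilot study, the sample size was primarily determined based on implementation feasibility". It adds that a non-significant interaction test need not exclude a meaningful interaction, and that findings will be read through effect sizes, confidence intervals, adherence and feasibility. It also keeps a conventional threshold: "All statistical tests will be two-sided, and a *p* value of < 0.05 will be considered statistically significant".

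No other section shown describes the trial as a pilot. Section 2.9.3 uses the word only for calibrating the raters on ten videos, and the title page is not shown. The abstract, the aims (1.2), the design (2.1) and the discussion describe an effectiveness trial. The abstract's discussion, for example, says: "The expected findings will provide more practical and effective intervention strategies for CPR training among middle school students".

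**The concern.** A sample size has one main basis. If 160 is the smallest number that gives the stated power for the primary effect, it was not determined primarily by feasibility. If feasibility determined it, 2.10 should not present it as a powered minimum.

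The choice matters most for a null result. Under 2.10, a non-significant main effect comes from a trial said to be large enough to detect it, so it counts as evidence against an effect of the planned size. Under 2.13, the same result comes from a pilot and is inconclusive. Nothing in the document says which reading applies, so it is not fixed before the data are seen.

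The statement that 160 suffices also uses one 25% allowance for two separate losses.

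**Working it through.** **Inputs from 2.10:** alpha 0.05 (two-sided per 2.13), power 0.80, f = 0.25, N = 128, attrition 20%, final N = 160, four classes of 40, design effect at most 1.25, with DE = 1 + (m − 1)ρ.

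**1. Reproducing the plan's figures.** For a one-degree-of-freedom effect in a four-cell layout, the noncentrality is λ = f² × N.
- N = 128: λ = 0.0625 × 128 = 8.0, with 1 and 124 degrees of freedom. Power is 0.801, and 128 is the smallest N that reaches 0.80.
- The critical F is 3.918, against 3.921 in the plan, a trivial difference.
- Attrition: 128 / (1 − 0.20) = 160.

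So the power calculation plus attrition fully accounts for 160. This agrees with 2.10 and sits badly with 2.13. It does not prove which consideration came first.

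**2. What the 25% allowance covers.**
- Attrition only: 160 × 0.80 = 128.
- Design effect only: 160 / 1.25 = 128.
- Both: 160 × 0.80 / 1.25 = 102.4 effective participants. Then λ = 0.0625 × 102.4 = 6.4 and power is about 0.71.
- Students needed for 0.80 with both: 128 × 1.25 / 0.80 = 200.

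Either loss alone uses the whole allowance.

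**3. Sensitivity to the design effect.** With m = 40, a ceiling of 1.25 implies ρ = 0.25 / 39 = 0.0064. Because the plan gives no ICC, the values below are assumptions, applied to 32 completers per class (40 × 0.80):

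| Assumed ICC | Design effect | Effective N | Power for f = 0.25 |
|---|---|---|---|
| 0.001 | 1.03 | 124 | 0.79 |
| 0.0064 | 1.20 | 107 | 0.73 |
| 0.01 | 1.31 | 98 | 0.69 |
| 0.02 | 1.62 | 79 | 0.59 |
| 0.05 | 2.55 | 50 | 0.41 |

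The second row applies the plan's implied ICC to the smaller completed classes, which softens 0.71 to 0.73. Power is below 0.80 in every row.

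**4. Limit of this arithmetic.** Sections 2.4.2 and 2.10 give one class per factorial cell. The design-effect formula shrinks the number of students but does not reflect having only four clusters, so all of these powers are optimistic.

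**The case against.** **The two sections address different effects.** Section 2.10 powers a main effect, while the caveat in 2.13 concerns interactions and is statistically correct: a non-significant interaction does not exclude a meaningful one, whether or not the trial is a pilot. This stands for the caveat. It does not rescue the sentence before it, which describes the whole study and the whole sample size without that limit.

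**The planned effect is larger than f = 0.25.** Section 2.10 also assumes d = 1.0, which for two equal groups is f = 0.5 and needs only about 34 students without clustering. On that effect, 102 effective participants would be ample at the individual level. The shortfall shown here is therefore for f = 0.25, the value that produced 128. The mismatch between the two effect sizes is a separate matter.

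**The abstract's language is only aspirational.** Agreed. It shows that pilot status is not carried through, but says nothing about how 160 was set.

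Three stronger readings are tempting, and the document does not support them:

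- *A significant result would be reported as confirmatory and a non-significant one excused as a pilot.* The document does not say so. Its only explicit softening for non-significance concerns interactions, and its general rule on interpretation does not exempt significant results.
- *The trial breaks a promise of power for the interaction.* Section 2.10 claims none. A power of about 0.29 can be computed at N = 128 for an interaction of 0.5 SD without clustering, but the plan states no such interaction; at 1.0 SD the same calculation gives 0.80.
- *Feasibility really set 160, or really did not.* The arithmetic fits the power account, but only the sponsor knows the true basis.

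**Conclusion.** The concern holds in this form: 2.10 and 2.13 give incompatible bases for the sample size and for the status of the trial, and this leaves the meaning of a null result open. Independently, 2.10's statement that 160 meets the requirement for the primary effect is not supported by its own inputs. With 20% attrition and a design effect of 1.25 together, power for f = 0.25 is about 0.71, not 0.80, and 200 students would be needed.

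These figures assume that attrition reaches the planned 20%, that the design effect is at its stated ceiling, and that the individual-level formula applies. The last assumption favours the plan, because there is one class per cell. The incompatibility of the two sections rests on no numerical assumption.

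**What to change.** 1. The sponsor should state one status (powered trial or pilot) and the one true basis for 160, and use them consistently in the abstract, 2.1, 2.10, 2.13 and the discussion.
2. Under either status, delete or restate the sentence in 2.10 that claims adequacy for the primary effect. Present 128 only as an individual-level reference for a main effect of f = 0.25 without clustering.
3. If pilot status is kept, label the trial a pilot throughout, and say that significant and non-significant results alike will be read as preliminary estimates with 95% confidence intervals.
4. State that the sample size calculation does not cover the interaction. Do not add a power figure for it, since the plan specifies no interaction size and such a figure would ignore clustering.

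The cost is wording in five places and a less favourable stated claim. No extra students or data are needed.

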**Methods:**

A single-blind cluster randomized controlled trial with a 2 × 2 factorial design will be conducted in a middle school in Hohhot, Inner Mongolia Autonomous Region. A total of 160 eligible middle school students will be recruited and randomly assigned in a 1:1:1:1 ratio to four groups: conventional CPR training group, manikin-based training group, scenario-based drama review group, and combined manikin-based training plus scenario-based drama review group. Each training session will last 90 min. The primary outcomes are CPR-related knowledge score and skill performance score. Secondary outcomes include self-efficacy (behavioral performance and evaluation), behavioral intention, course satisfaction, and skill retention rate. Data will be collected at Baseline assessment (T0), immediate post-first training assessment (T1), 3-month post-first training assessment (T2), immediate post-second training assessment (T3), 3-month post-second training follow-up (T4).

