### Study design and settings

2.1

This study is designed as a single-center, single-blind, 2 × 2 factorial cluster randomized controlled trial involving middle school students aged 11–18 years. The trial will be conducted in a middle school in Hohhot, Inner Mongolia Autonomous Region. This study setting offers favorable implementation conditions and organizational advantages: cluster allocation based on existing classes aligns with routine educational management, facilitates standardized delivery of training and follow-up assessments, and effectively reduces contamination associated with individual randomization, thereby enhancing both feasibility and internal validity. The factorial design allows for the independent evaluation of the main effects of manikin-based training and scenario-based drama review, as well as their interaction effect. This study includes Baseline assessment (T0), immediate post-first training assessment (T1), 3-month post-first training assessment (T2), immediate post-second training assessment (T3), 3-month post-second training follow-up (T4), to evaluate the short-term and long-term effects of the intervention.

This study was approved by Inner Mongolia Maternal and Child Health Care Hospital Approval Form of the Medical Ethics Committee [File No (2025) Lunshen K No. (021-1)].

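### The primary endpoint is stated in two ways, no time point is primary, and every test uses p < 0.05, so the 5% error rate in the sample size section does not hold for the primary claim

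*Protocol article*

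**What the plan says.** **Outcomes.** The abstract (Methods) states: "The primary outcomes are CPR-related knowledge score and skill performance score". It gives no order between the two and no rule that both must succeed. Section 2.10 speaks of a single primary outcome and bases its assumptions on a "combined knowledge and skills score rate". Sections 2.8.1 and 2.8.2 define knowledge (0 to 9) and skills (eight components, no range given) separately. No section says how to combine them. Section 2.13 again refers to one primary outcome.

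**Factors.** Section 2.13: "Two binary intervention factors are specified", namely initial training method and "Factor 2, booster reinforcement method".

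**Times.** Sections 2.1 and 2.11 set four assessments after baseline, T1 to T4. T2 comes before the second training session. None of the four is named primary.

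**Route through the tests.** Section 2.13 begins with interactions, including that "the three-way interaction among the two intervention factors and time within the repeated-measures framework will first be tested". If an interaction is significant, or shows a trend of practical importance (not defined), simple effects at each time point follow. Otherwise the two main effects are interpreted. Factor-by-time terms are also treated as key parameters.

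**Threshold.** Section 2.13: "All statistical tests will be two-sided", with p below 0.05 counted as significant. The article states no multiplicity adjustment, alpha split or ordering of outcomes.

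**The concern.** Section 2.10 spends the whole 5% on one main-effect test of one combined score. The analysis described elsewhere has two scores, two factors, several times and a data-dependent choice between main effects and per-time effects, each judged at 0.05. A reader of the final report could not tell which result was meant to carry the claim of effectiveness. A single nominal p < 0.05 on one score, for one factor, at one time could be presented as the primary finding with a false-positive risk well above the planned 5%. This rests on what the article states (two incompatible primary endpoints and one threshold for all tests), not only on detail that an analysis plan might add.

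**Working it through.** **1. The plan's own figure.** Section 2.10 gives N = 128 for effect size f = 0.25, alpha 0.05 and power 0.80, then 160 after 20% attrition.
- Noncentrality = N × f² = 128 × 0.0625 = 8.
- With 1 and 124 degrees of freedom (four groups), critical F = 3.918 and power = 80.1%. The stated critical F of 3.921 corresponds to 119 denominator degrees of freedom. N is 128 either way.
- 128 / 0.80 = 160.

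The figure reproduces, and it belongs to one test at the full 5%.

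**2. Inputs for the error rate.**
- From the article: 2 outcomes, 2 factors, 4 post-baseline times, two-sided 0.05 per test.
- Assumed, because the article gives no values: correlation 0.5 between the two outcomes and 0.5 between times, with ranges shown below. The two factors are taken as independent, as in a balanced factorial.
- Also assumed: each test holds its nominal 5%.
- Interaction tests are not counted.

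**3. One time point.** With independent outcomes, the chance of at least one p < 0.05 for one factor is 1 − 0.95² = 9.75%. With simulated correlated z-statistics:

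| Outcome correlation | Per factor | Both factors, 1 − (1 − p)² |
|---|---|---|
| 0.3 | 9.5% | 18% |
| 0.5 | 9.1% | 17% |
| 0.7 | 8.3% | 16% |

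At 0.5: 1 − (1 − 0.091)² = 0.17.

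**4. T3 and T4 both used.** Two outcomes at two times give about 16.2% per factor (simulated, both correlations 0.5). Over both factors: 1 − (1 − 0.162)² = 0.30.

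**5. Each factor read only where it can act.** Factor 2 is the booster and T2 precedes it, so Factor 2 has no effect to show at T1 or T2. Factor 1 at T1 to T4 gives about 26.8% (simulated, both correlations 0.5), and Factor 2 at T3 and T4 about 16.2%. Together: 1 − (1 − 0.268)(1 − 0.162) = 0.39. With both correlations between 0.3 and 0.7, the result runs from 43% down to 32%.

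**6. Status of steps 4 and 5.** They count every factor-by-time test as if it were always run. Section 2.13 makes per-time simple effects conditional, so they are upper counts of those tests. Section 2.11 also says that T4 collects only questionnaires while listing a skills score there, so the number of skills times is itself unclear. Step 3 needs no per-time testing.

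**7. Power cost of an adjustment.** At alpha 0.025, with N = 128 and f = 0.25, critical F = 5.148 and power = 71.2%, against 80.1% at 0.05.

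**The case against.** **The plan does not say that any success counts.** A reader might infer that a result on either outcome, for either factor, at any time would be claimed. No section says so. Section 2.13 sets an order and says that findings will be weighed with effect sizes and confidence intervals. This stands, and it is why the wider figures are upper counts. However, the trigger for per-time analysis includes an undefined trend, so the order restrains the choice only loosely.

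**A chance positive is not shown to be likely.** A reader might also infer that a false-positive primary result is more likely than not. The figures above do not support that: all are below one half. Counting Factor 2 at all four times would give about 46% at correlations of 0.5, but that includes tests made before the booster is given.

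**Factors in a factorial trial are often treated as separate questions.** On that view the relevant figure is about 9%, not 17%. That is a fair position, and the fix below adopts it. Even 9% is nearly double the planned rate.

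**It is a pilot, and an analysis plan may exist.** Section 2.13 does call the trial a pilot. Yet 2.10 gives a confirmatory alpha and power calculation for the primary effect, and 2.13 keeps a p < 0.05 rule. An unseen plan could add an adjustment, but it would not remove the contradiction between the abstract and 2.10.

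**Nominal 5% may not hold anyway.** With one class per arm, class and arm are confounded, so each test's true error may exceed 5%. This is correct. It makes the figures above doubtful, and probably too low.

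**Conclusion.** The point holds in this form: the primary endpoint is contradictory, no time point is primary, and an unadjusted 0.05 applies throughout, so the 5% in section 2.10 does not describe the primary claim. At a single time the error is about 9% per factor (8% to 9.5% for outcome correlation 0.7 to 0.3) and about 17% over both factors. The 30% and 39% figures are what the open choice of time could add at most, on the factor-by-time tests counted. All of these rest on assumed correlations and on each test holding its nominal level. The defect should be corrected before analysis. It does not show that a positive result would be false.

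**What to change.** 1. Reconcile the abstract with section 2.10, so that both state the same primary outcome or outcomes.
2. Name one primary time point after both components have been delivered. T3 is the first such visit. If long-term retention matters more, T4 could be chosen instead, once section 2.11 makes clear whether skills are measured there.
3. Within each factor, either (a) apply Holm across the knowledge and skills scores, or (b) make the combined score the single primary outcome and state its formula and weighting.
4. Label the other times, the interactions and the secondary outcomes as supportive.

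**Cost.** Option (a) needs only wording, but Holm's first step at 0.025 lowers individual-level power at N = 128, f = 0.25 from 80% to about 71% in the worst case. Option (b) avoids that loss but means specifying an endpoint that the article does not yet define. Either option controls error within each factor. Across both factors it can still reach 1 − 0.95² = 9.75%, which the plan should accept openly. Holding 5% over two outcomes and two factors by an equal split (0.0125 each) would reduce power to about 62%. None of these power figures includes clustering, and Holm does not repair the separate confounding of class with arm.
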